## Abstract

**Background:**

Chemoradiotherapy (CRT) with concurrent cisplatin is the standard of care as a nonsurgical definitive treatment for patients with locally advanced squamous cell carcinoma of the head and neck (LA-SCCHN). However, CRT is associated with increased severe late adverse events, including swallowing dysfunction, xerostomia, ototoxicity, and hypothyroidism. Few strategies aimed at less invasive CRT without compromising treatment outcomes have been successful. The purpose of this study is to confirm the non-inferiority of reduced dose prophylactic radiation with 40 Gy compared to standard dose prophylactic radiation with 56 Gy in terms of the time to treatment failure (TTF) among patients with clinical stage III-IVB LA-SCCHN.

**Methods:**

This study is a multicenter, two-arm, open-label, randomized phase III trial. Patients with LA-SCCHN excluding p16 positive oropharynx cancer are randomized to the standard arm or experimental arm. A total dose of 70 Gy for tumors with concurrent cisplatin at 100 mg/m^2^ are administered in both arms. For prophylactic field, patients in the standard arm receive a total dose of 56 Gy in 35 fractions for 7 weeks using simultaneous integrated boost (SIB56) and those in the experimental arm receive 40 Gy in 20 fractions using two-step methods for 4 weeks (2-step40). A total of 400 patients will be enrolled from 52 Japanese institutions within 5 years. The primary endpoint is TTF, and the secondary endpoints are overall survival, complete response rate, progression-free survival, locoregional relapse-free survival, acute and late adverse events, quality of life score, and swallowing function score.

**Discussion:**

If the experimental arm is non-inferior to the standard arm in terms of TTF and superior on the safety endpoints, the 2-step40 procedure is the more useful treatment than SIB56 for definitive CRT.

**Trial registration:**

This trial has been registered in the Japan Registry of Clinical Trials as jRCTs031210100 (https://jrct.niph.go.jp/latest-detail/jRCTs031210100). Date of Registration: May 2021.

**Supplementary Information:**

The online version contains supplementary material available at 10.1186/s12885-023-11503-z.

## Background

Chemoradiotherapy (CRT) with concurrent high-dose cisplatin (CDDP) is a standard treatment for patients with locally advanced squamous cell carcinoma of the head and neck (LA-SCCHN) [1–4]. However, CRT is associated with increased severe late adverse events, including swallowing dysfunction, nephrotoxicity, neurotoxicity, ototoxicity, and hypothyroidism [5–7], most of which are irreversible and likely to reduce quality of life in patients treated with CRT [8]. Furthermore, long-term results of the Intergroup Radiation Therapy Oncology Group 91 − 11 study revealed an unexplained increase in deaths unrelated to cancer in patients who received concomitant cisplatin plus radiotherapy (RT) [9].

Intensity-modulated radiation therapy (IMRT) has emerged as a current standard method for definitive CRT for LA-SCCHN. Although the advantage of IMRT is its highly conformal dose distribution to the primary tumor and involved lymph nodes with sufficiently low exposure to organs at risk, severe late adverse events after CRT remain a significant problem to be resolved.

Several strategies aiming at less invasive CRT using IMRT for LA-SCCHN have been investigated, including (i) reducing the total irradiation dose, (ii) alternative concurrent pharmacotherapy to CDDP, and (iii) reducing the irradiation dose in prophylactic field. However, an increase in local recurrence by using reduced total dose radiation was noted even in HPV-positive oropharyngeal cancer with favorable clinical outcomes [10, 11]. The combination of cetuximab, an epidermal growth factor receptor − targeting monoclonal antibody, and radiation therapy had inferior therapeutic efficacy to CDDP plus RT, with the similar frequency of feeding tube dependency to CRT because of the high incidence of mucositis [12, 13]. Therefore, we focus on dose reduction in prophylactic field irradiation.

A randomized controlled trial was conducted to investigate reduction of the dose of RT to the elective nodal sites, with 50 Gy in the standard arm and 40 Gy in the experimental arm. The results revealed a trend toward less dysphagia at 6 months in the 40 Gy arm though not statistically significant (38.4% vs. 48.6%), without compromising outcome and survival [14]. However, a large heterogeneity remains in terms of irradiation schedule and prescription, and the use of concurrent chemotherapy.

Based on these backgrounds, we have launched a randomized controlled trial to confirm the non-inferiority of reduced dose prophylactic radiation with 40 Gy using two-step40 IMRT method (2-step40) to standard dose prophylactic radiation with 56 Gy using simultaneous integrated boost (SIB56) in terms of the time to treatment failure for patients with clinical stage III-IVB (except N3a) LA-SCCHN according to UICC-TNM 8th .

## Methods/design

### Study design

This study is a multi-institutional, two-arm, open-label, randomized phase III study. The study protocol was reviewed by the Japan Clinical Oncology Group (JCOG) Protocol Review Committee and approved by as the JCOG1912 (NEW BRIDGE) in January 2021. The certificated review board approved in March 2021, and patient accrual was started at May 2021. The trial registry number is jRCTs031210100 (https://jrct.niph.go.jp/latest-detail/jRCTs031210100).

### Endpoints

The primary endpoint is time to treatment failure (TTF) 1 in all randomized patients. TTF1 is defined as time from randomization to the date of progression, or determination of residual disease after the completion of the protocol treatment, or death from any cause, whichever occurred first, and it is censored at the last day the patient is alive without any evidence of progression. The secondary endpoints are overall survival (OS), complete response rate, progression-free survival (PFS), locoregional relapse-free survival, TTF2, acute and late adverse events, quality of life (QOL) score, and swallowing function score. OS is defined as the time from randomization to death from any cause and is censored on the last contact day for a surviving patient. PFS is defined as the time from randomization to the earliest date of progression or death from any cause and is censored on the last contact day when the patient is alive without any evidence of relapse. In the definition of TTF2, clinical residual disease in TTF1 events is not regarded as an event or censor of TTF2, if complete resection is conducted by salvage surgery and subsequent histopathological examination reveals pathological complete response.

### Eligibility criteria

The inclusion criteria are as follows:

(i)Primary lesions are located in the oropharynx, hypopharynx, or larynx.(ii)Histologically proven squamous cell carcinoma on biopsy specimens of the primary lesion. Immunohistochemistry reveals p16 negativity in patients with oropharyngeal cancer.(iii)Clinical stage of III, IVA, or IVB (excluding N3a) based on the 8th UICC-TNM classification.(iv)Age of ≥ 20 years.(v)Eastern Cooperative Oncology Group performance status of 0 or 1.(vi)Measurable lesions are not required.(vii)No prior chemotherapy for any cancers and no prior RT for brain, head or neck lesions. No prior surgery for head and neck cancers, except for a biopsy of neck lymph nodes for a diagnosis.(viii)Any of the following conditions:

Both the primary lesion and regional lymph node metastases are technically or functionally unresectable. Tumor resectability will be determined through a review by a head and neck surgeon.Although the tumors are resectable, patients do not wish to undergo surgical resection.

(ix)Adequate organ function.

Neutrophil ≥ 1,000/mm^3^.Hemoglobin ≥ 9.0 g/dL.Platelet ≥ 100,000/mm^3^.Total bilirubin ≤ 2.0 mg/dL.Aspartate aminotransferase ≤ 100 U/L.Alanine aminotransferase ≤ 100 U/L.CCr ≥ 60 mL/min.

(xxiv)Written informed consent for participation.

Exclusion criteria.

(i)Synchronous or metachronous (within 5 years) double cancers, except for intramucosal tumors curatively resected with local therapy.(ii)Active infection requiring systemic therapy.(iii)Fever over 38.0 °C.(iv)Female during pregnancy, within 28 days of postparturition, or during lactation. Male who wants partner’s pregnancy.(v)Psychiatric disorder difficult to participate in this clinical study.(vi)Requirement of systemic steroid medication or immunosuppressant treatment.(vii)Poorly controlled diabetes mellitus.(viii)Poorly controlled hypertension.(ix)Unstable angina within 3 weeks or with a history of myocardial infarction within 6 months before trial enrollment.(x)Poorly controlled valvular disease, dilated cardiomyopathy, or hypertrophic cardiomyopathy.(xi)Positive hepatitis B surface antigen test.(xii)Positive human immunodeficiency virus antibody test.(xiii)Inability to quit smoking and drinking.

### Randomization

After eligibility has been confirmed, registration is performed using a web-based system at the JCOG Data Center. Patients are randomized to the standard arm (SIB56) or experimental arm (2-step40). Randomization is stratified according to the institution, presence or absence of lymph nodes metastasis, and the primary sites (oropharynx vs. hypopharynx vs. larynx).

### Treatment methods

Patients in both arms receive definitive CRT with CDDP at a dose of 100 mg/m^2^ on days 1, 22, and 43. IMRT is administered at a total dose of 70 Gy given for tumor in single, daily, 2 Gy fractions for 7 weeks in both arms. For prophylactic field, patients in the standard arm receive a total dose of 56 Gy in 35 fractions for 7 weeks, and those in the experimental arm receive 40 Gy in 20 fractions for 4 weeks (Fig. 1) [15].

**Fig. 1 Fig1:**
[figure not shown]
Study scheme. SCCHN, squamous cell carcinoma of the head and neck; CDDP, cisplatin; SIB, simultaneous integrated boost

Radiation planning is performed 2 weeks before the start of RT. The cervical computed tomography (CT) is performed using a thermoplastic mask for fixation. In the 2-step40 method group, another planning CT scan is performed at a dose of 30 Gy per the boost IMRT plan. RT is delivered with 4–10 MV photons using IMRT at a total dose of 70 Gy in 35 fractions over 7 weeks in both arms. The gross tumor volume (GTV) is defined as the volume of the primary tumor and the metastatic lymph nodes measuring 10 mm along the short axis. The clinical target volume (CTV) includes the GTV with a 0.5- 1- cm margin. The regional lymph nodes include the bilaterally cervical lymph nodes, and details on the prophylactic field are determined according to the primary site [16]. The planning target volume (PTV) is defined as CTV plus a 0.5-cm margin to account for organ motion and daily set-up errors. Organs at risk (OAR) was defined as the spinal cord, brainstem, parotid gland, mandible, inner ear, thyroid gland, oral cavity, pharyngeal constrictor muscle, and larynx. The dose constraint of PTV and OAR are defined in the protocol, and quality assurance of radiation planning of all registered patients is mandatory.

### Assessment and follow-up

Before CRT, routine oral screening by dentists, head and neck endoscopy, and esophagogastroduodenoscopy are performed. All patients should receive baseline evaluation of swallowing function, hearing function, and QOL. Swallowing function is assessed by performing a videoendoscopic evaluation of swallowing and using Functional Outcome Swallowing Scale (FOSS). The hearing function is evaluated using pure-tone audiometry. The Core Quality of Life questionnaire (QLQ-C30) and Quality of Life Questionnaire Head and Neck Module (QLQ-HN43) scales are used for the QOL evaluation.

During protocol treatment, evaluations of general and performance statuses, safety profile according to the Common Terminology Criteria of Adverse Events (CTCAE) version 5.0, and blood examinations are performed at least weekly.

The initial efficacy assessment using enhanced CT for the cervix, chest, and abdomen, and magnetic resonance imaging (MRI) of the head and neck region are performed 16 weeks (± 4 weeks allowed) after the start of treatment. If there is a contrast effect secondary to tumor shrinkage (scarring), Positron Emission Tomography (PET)-CT should be performed 4 weeks (± 1 week allowed) after the initial efficacy evaluation because of the difficulty in determining efficacy. A biopsy is recommended if macroscopic residual disease is suspected. If the biopsy is positive, or if there is positive FDG uptake by PET-CT as well as corresponding lesions confirmed on MRI/CT, or if there is evidence of progression, salvage surgery is considered. Primary lesion excision and/or neck dissection is performed as salvage surgery depending on the lesion.

Patients’ general status, acute and late toxicities, blood examination including thyroid function, enhanced CT and MRI are periodically performed every 16 weeks in the first 2 years, and every 24 weeks from the second to the third year after the initiation of protocol treatment. Evaluations of swallowing and QOL are performed at 16 weeks, and 1, 2, and 3 years after the initiation of the protocol treatment. Evaluation for hearing function is performed at 1 year and 3 years after initiation of protocol treatment. The precise assessment schedule from pretreatment to 3 years after initiation of the protocol treatment is shown in Table 1.

**Table 1 Tab1:** Study calendar

	Pretreatment	During treatment	− 90D^b^	91D − 2Y^c^	2Y – 3Y^d^	16 W	1Y	2Y	3Y
Physical examination	○	△^1 W^	◎	△^16 W^	△^24 W^				
PS	○	△^1 W^	◎	△^16 W^	△^24 W^				
CT/MR	○			△^16 W^	△^24 W^				
Blood examination^a^	○	△^1 W^	◎	△^16 W^	△^24 W^				
Safety profile		△^1 W^	◎	△^16 W^	△^24 W^				
Body weight	○	○	◎			○	○	○	○
Nutrition access	○						○	○	○
Swallowing function	○					○	○	○	○
Pure Tone Audiometry	○						○		○
QOL	○					○	○	○	○

^a^Including thyroid stimulating hormone (TSH) and thyroxine

^b^From end of protocol treatment to 90 days after initiation of protocol treatment

^c^From 91 days to 2 years after initiation of protocol treatment

^d^From 2 years to 3 years after initiation of protocol treatment

*CT *Computed tomography, *MRI *Magnetic resonance imaging, *QOL *Quality of life

△1 W: every week, △16 W: every 16 week,△24 W:every 24 week, ◎;at least every 2 week within 28 days after the end of chemoradiotherapy, but at least every 4 week 29 days after the end of chemoradiotherapy

### Statistical analysis and evaluation criteria for the endpoints

A 3-year TTF1 of 50% is assumed for both arms. According to the Schoenfeld and Richter’s method [17], the required sample size has been calculated as 197 patients per arm, with a study-wise one-sided alpha level of 5%, a power of 75%, and a non-inferiority margin of 10% (hazard ratio = 1.32). A total of 400 patients will be included within 5 years, and all randomized patients will be followed up for at least 5 years after the patient recruitment is completed. The primary endpoint is analyzed 3 years after recruitment has been completed. All statistical analyses will be conducted at the JCOG Data Center.

If the experimental arm is non-inferior to the standard arm in terms of TTF1 and superior in terms of safety endpoints, the 2-step40 method will be considered the more efficacious treatment. However, it is unacceptable that a point estimate of 3-year OS in the experimental arm is more than 5% lower than that in the standard arm. Based on mathematical models, the rates of key late adverse events of grade 2 or higher are expected to be reduced by approximately 15%, 7%, 7%, and 10% for hearing impairment, hypothyroidism, dry mouth, and dysphagia, respectively. If the experimental arm shows sufficient improvement in at least one of these key late adverse events, the study treatment will be considered as beneficial. If the non-inferiority of the experimental arm in terms of the primary endpoint is not demonstrated, the SIB56 method will be considered a useful treatment.

### Interim analysis and monitoring

Two interim analyses considering multiplicity will be conducted using the Lan and DeMets method along with the O’Brien and Fleming-type alpha spending function [18]. The first interim analysis will be conducted after half of the planned number of patients are enrolled, and the second interim analysis will be performed after the planned patient recruitment is completed. The Data and Safety Monitoring Committee of the JCOG will review the interim analysis report independently from the group investigators and group statisticians.

In the first interim analysis, if both the non-inferiority and superiority of the experimental arm over the standard arm in terms of the primary endpoint are demonstrated with an adjusted alpha level, the study will be terminated. If the non-inferiority of the experimental arm at the primary endpoint is not demonstrated or its non-inferiority but not superiority is demonstrated, the study will be continued. In the second interim analysis, the study will be terminated if the non-inferiority of the experimental arm to the standard arm in the primary endpoint is demonstrated with an adjusted alpha level. If the non-inferiority of the experimental arm in the primary endpoint is not demonstrated, the study will be continued. In both interim analyses, if the point estimate of the hazard ratio of TTF1 exceeds the non-inferiority margin (1.32), the study will be terminated because of futility.

In-house monitoring will be performed every 6 months by the JCOG Data Center to evaluate and improve study progress, data integrity, and patient safety. All enrolled patients are evaluated for compliance with the RT protocol at the time of completion of RT. The purpose of this assessment is to confirm whether the actual treatment at each participating institution is performed according to the protocol regulations and to provide feedback for the treatment of subsequently enrolled patients.

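### The stated 75% power takes no account of the mandatory futility stop at an interim hazard ratio above 1.32; with it, power is about 66% on the plan's own assumptions, and up to about 71% with later data cuts

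*Protocol article*

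**What the plan says.** The design assumptions are in the protocol article, under Statistical analysis and evaluation criteria for the endpoints. "A 3-year TTF1 of 50% is assumed for both arms", so the power is computed at a true hazard ratio of 1. Under the Schoenfeld and Richter method, "the required sample size has been calculated as 197 patients per arm", for "a study-wise one-sided alpha level of 5%, a power of 75%, and a non-inferiority margin of 10% (hazard ratio = 1.32"). The recruitment target is 400 over 5 years, and the primary analysis takes place 3 years after recruitment ends.

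Interim analysis and monitoring sets two looks with Lan-DeMets, O'Brien-Fleming-type spending. "The first interim analysis will be conducted after half of the planned number of patients are enrolled", and the second look follows the end of recruitment. At both, "if the point estimate of the hazard ratio of TTF1 exceeds the non-inferiority margin (1.32), the study will be terminated because of futility". The rule is worded as mandatory and uses the point estimate alone. The article gives no expected or minimum number of events for either look.

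**The concern.** The power statement and the futility rule stand in adjacent sections, but the first does not appear to reflect the second. A rule that ends the trial whenever the estimate passes the margin removes some trials that would have gone on to show non-inferiority. How many depends on the information available at the look. A look fixed by enrolment comes early in terms of events, so an estimate above 1.32 can arise by chance when the arms are equal.

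At stake is the probability that the trial confirms a regimen that is in fact equivalent. The planned figure is only 75%, so there is little to spare.

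**Working it through.** **1. Reproduce the plan's figure.**
- Margin: ln(ln 0.40 / ln 0.50) = ln 1.3219 = 0.2791.
- Events: 4 × (1.645 + 0.6745)² / 0.2791² = 276.3, so 277.
- Event probability with exponential TTF1, λ = ln 2 / 3 = 0.2310, accrual A = 5 and follow-up F = 3: 1 − [e^(−λF) − e^(−λ(A+F))] / (λA) = 1 − (0.5000 − 0.1575) / 1.155 = 0.7035.
- Patients per arm: 277 / 0.7035 / 2 = 196.9, so **197**, as stated.

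This is a fixed, single-look calculation. With 400 patients its power is 75.3%.

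**2. Expected events at each look** (N = 400, uniform accrual, data cut when the enrolment trigger is met).
- Look 1, year 2.5: 200 × 0.2404 = 48.1 (17% information).
- Look 2, year 5: 400 × 0.4070 = 162.8 (58%).
- Final, year 8: 400 × 0.7035 = 281.4.

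**3. Chance of a futility stop at true HR = 1.** The standard error of the log hazard ratio is about 2/√events.
- Look 1: SE = 2/√48.1 = 0.288; 1 − Φ(0.2776 / 0.288) = **16.8%**.
- Look 2: SE = 2/√162.8 = 0.157; 1 − Φ(0.2776 / 0.157) = 3.8%. Of this, 1.5 points are trials not already stopped at look 1.
- Either look: 18.3%.

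**4. Power.** Joint normal distribution of the three estimates, with one-sided 5% O'Brien-Fleming-type bounds Z = 4.60, 2.33 and 1.675, by simulation of 2 to 3 million paths:

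| Futility rule | Power at HR = 1 |
|---|---|
| None | 75% |
| Second look only | 75% |
| Both looks, as written | **66%** |

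About 52% of the trials stopped at look 1 would otherwise have shown non-inferiority (0.168 × 0.52 ≈ 9 points), so nearly all the loss arises there. A patient-level Cox simulation under the same assumptions gives about 65%.

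**5. Sensitivity to what the article does not state.**

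| Scenario | Events at look 1 | Stopped at look 1 | Power without → with rule |
|---|---|---|---|
| Exponential, cut at patient 200 | 48 | 17% | 75% → 66% |
| Exponential, both cuts 6 months later | 67 | 13% | 75% → 69% |
| Exponential, both cuts 12 months later | 88 | 10% | 74% → 71% |
| Weibull shape 0.6, cut at patient 200 | 63 | 14% | about 70%, loss about 5 points |

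With the Weibull shape and cuts 6 or 12 months later, the loss is about 3 or 1.5 points.

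**6. Type I error.** At true HR 1.32, one-sided error is about 4.2% with the rule at both looks, and about 4.9% if the first-look threshold is 1.8. Both are below 5%.

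**7. What the first look protects against.** Probability of stopping at look 1 with 48 events:

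| True HR | Threshold 1.32 | Threshold 1.8 | No rule at look 1 |
|---|---|---|---|
| 1.0 | 17% | 2% | 0 |
| 1.32 | 50% | 14% | 0 |
| 1.5 | 67% | 26% | 0 |
| 1.7 | 81% | 42% | 0 |

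**The case against.** The strongest reply is that this is a legitimate trade. In a de-escalation trial, stopping early when the reduced dose looks worse protects patients, and the rule can only lower type I error, so any claim of non-inferiority stays valid. That stands. A reader might infer from the demanding efficacy bound at look 1 (for superiority, an observed hazard ratio below about 0.27) that this look can only stop the trial wrongly or let it continue. The last table in the working shows otherwise: the look stops half or more of the trials in which the true hazard ratio is 1.32 or higher.

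A second reply is that 66% is not a figure in the documents. This also stands in part. The 17% information rests on exponential failure, uniform accrual and a data cut at patient 200. TTF1 counts residual disease, with the first efficacy assessment at about 16 weeks, so failures may well be front-loaded, and a cut could come later. The size of the loss is therefore a range, although every scenario tried shows one.

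A third reply is that the full protocol may report the rule's operating characteristics. It may, and nothing here shows that the sponsor failed to evaluate the rule. But the published 197 is fully explained without any allowance for it.

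**Conclusion.** The 75% is the power of a single-look design and is not what the described design delivers if the futility rule is followed. Under the assumptions that reproduce 197 per arm, with the data cut at patient 200, power at true HR = 1 is about 66%, and a truly equivalent regimen is stopped at half enrolment about one time in six. Across the variants examined, the rule costs about 1.5 to 9 points. The lower losses need late cuts or front-loaded failures, and the front-loaded case starts from about 70% rather than 75%.

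The direction of the effect is firm; the exact figure depends on timing and hazard shape. The documents do not support reading this as inflated type I error, or as proof that the first-look rule is wrong in itself. What needs correcting is the power statement. Whether to change the rule is for the sponsor to weigh.

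**What to change.** **Needed.** Restate the power with the futility rule included: about 66%, or 66% to 71% depending on the data cut. State the events expected at each look, the data-cut convention and the assumed failure distribution. This costs a wording change and no patients.

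**Optional, if about 75% is to be kept.**
- Apply the 1.32 point-estimate rule at the second interim only: power about 75%. Cost: no futility stop at half enrolment, against 50%, 67% and 81% stopped now at true HR 1.32, 1.5 and 1.7.
- Use a first-look threshold suited to about 48 events, for example about 1.8: 2% false stops and power about 74%. Cost: first-look stopping falls to 14%, 26% and 42% at the same three hazard ratios.

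Either option needs an amendment and notice to the Data and Safety Monitoring Committee, with these stopping probabilities set beside the power so that the trade is explicit. The article says only that the committee reviews the interim report. It should not be assumed to replace the protection given up unless a harm criterion is written down.
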